**Methods:**

Biofeedback therapy using Cerebri for the prevention of migraine attacks in adults with episodic migraine (The BioCer study) is an open-label, randomized, waitlist-controlled, multicenter trial. This study investigates the safety and efficacy of daily home-based biofeedback sessions using the Cerebri device. A total of 286 participants will be randomized to either a 12-week intervention arm or waitlist control arm. The primary outcome is the change in the mean number of migraine days from baseline to the last 28-day period during the treatment phase in the treatment group compared with the control group. The primary outcome variable is prospectively collected through daily eDiary entries. A limitation is the inability to conduct a sham-controlled trial of biofeedback.

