**Figure 1. f1:**
[figure not shown]
Flow chart of the BioCer study.

Eligible participants are randomly allocated to the treatment or waitlist groups. The treatment group receives the medical device by postal service, and a treatment period of 12 weeks is initiated on the first day of completing a biofeedback session. Participants in the waitlist group complete daily eDiary entries for 12 weeks from the day of randomization.

Both arms are invited to participate for a 12-week extension period. Participants randomly allocated to the waiting list are offered the possibility of entering a 12-week extension phase with biofeedback treatment. The 12-week extension period is initiated on the first day of the biofeedback training. The participants randomized to the intervention group are invited to a 12-week extension period after completing their 12-week biofeedback treatment, in which they continue with daily eDairy only.

Participants will not have access to the intervention at the end of the study. Beyond the voluntary 12-week extension period, there will be no long-term follow-up on safety and survival status, except in cases of pregnancy.

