### Randomization and stratification

Random group allocation occurs a minimum of four weeks after inclusion and after rescreening. If eligible, permuted block randomization is performed. Randomization is stratified on the adjunct use of preventive medication.

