### Statistical analysis

Research hypothesis

The primary endpoint is to investigate the change in the mean number of migraine days from baseline to the last 28-day period in the treatment group compared with the wait-list control group. Thus, the null hypothesis (H0) and alternative hypothesis (H1) to be tested in relation to the primary objective are as follows.
•H0: The change in the mean number of migraine days from the 28-day baseline to the last 28-day period in the treatment group is equal to the change in the mean number of migraine days from baseline to the last 28-day period in the wait-list control group.

vs.
•H1: The change in the mean number of migraine days from the 28-day baseline to the last 28-day period in the treatment group is not equal to the change in the mean number of migraine days from baseline to the last 28-day period in the wait-list control group.

Sample size

The sample size calculation is based on an assumption of the effect size derived from a relevant meta-analysis of the efficacy of biofeedback in treating migraine
^
15
^ and a randomized pilot study.
^
9
^ Provided an effect size of d = 0.4, a significance level alpha of 0.05 (two-sided), power 0.8, and a dropout rate of 30% in the post-randomization period, the required sample size of this study was estimated to 286 participants. The anticipation of high dropout rates in this study is justified in the significant challenge of maintaining participant adherence observed in home-based mHealth studies.
^
9
^
^,^
^
16
^

Protocol deviations

Participants with incomplete or missing headache diary entries in more than 30% of days in the post-randomization period, participants with more than 30% missing or incomplete biofeedback sessions in the treatment arm, and participants initiating new or altering the use of their established preventive headache medications during the trial, are considered protocol deviators.

Statistical analysis plan

The statistical analysis plan (SAP) will include a technical and detailed description of statistical analysis. Statistical analyses will be conducted by an independent statistician. The analysis will follow a predefined order, where the primary efficacy endpoint is analyzed first. The trial statistician will analyze the efficacy outcomes without knowledge of treatment allocation by using a dataset with study arm allocation coded as groups A and B.

Data analysis set

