For the efficacy analysis, the full analysis set includes all randomized participants and constitutes the intention-to-treat (ITT) population. The per protocol (PP) population includes all randomized participants without protocol deviations.

Analysis dataset 1 is defined as the data from the 16-week period for all randomized participants and does not include extension period data. The 12-week post-randomization period in the biofeedback arm starts on the date of the first biofeedback session. Data lock for the evaluation of efficacy endpoints can be performed upon the completion of this dataset.

The safety data set includes all participants exposed to the biofeedback device.

Primary endpoint analysis

Analysis of the study endpoints will be performed in the ITT (all randomized subjects) and PP populations.

The primary endpoint variable is migraine days. The operational definition used for the analysis will be prespecified in the SAP.

The planned analysis strategy involves a mixed logistic regression model which will include all available daily eDiary entries. The mixed logistic regression model will be used to estimate the difference in the change from baseline in the mean number of migraine days per 28-day period between the treatment and waitlist groups. The model will include the presence or absence of migraine on each day from the baseline and 12-weeks post randomization periods as a dependent binary variable, treatment allocation, time period (baseline, week 1-4, week 5-8 and week 9-12) and an interaction term between treatment allocation and post-randomisation time-periods are included as categorical fixed effects, together with the stratification variable (concomitant preventive medication use). The patient ID will be included as a random effect. The site of inclusion will also be assessed as a potential random effect prior to the unblinding of the statistician to the treatment allocation. The model does not require explicit imputation, as mixed models yield unbiased estimates under the assumption that data are missing at random. This assumption will be assessed and sensitivity analyses considered if warranted.

The primary effect estimate will be the model-based estimates of the difference in change from baseline in mean monthly migraine days between the treatment and waitlist groups, presented with a 95% confidence interval.

Baseline variables that are considered to be highly predictive of outcomes will be discussed and identified

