*a priori* and described in the SAP. These variables will be included in multivariate analysis. The SAP will also detail the analysis strategies for the secondary outcomes. Post hoc stratified analyses by sex (women vs. men) and assessment of sex interaction will be conducted.

The statistical analysis plan includes predefined sensitivity analyses, restricting the primary analysis to the per-protocol set and, if feasible, subgroup analyses according to adherence status. Specifically:
•Participants in the interventional group with >90% biofeedback adherence in all three 28-day periods will be compared with the remaining participants in the interventional arm with lower adherence.•Participants in the interventional group with >90% adherence during weeks 1–4 will be compared with the remaining participants in the interventional arm with lower adherence in that same period.

Safety data

Safety objectives will be assessed by collecting data on treatment-emergent adverse events encountered during biofeedback training, including adverse events (AEs), serious adverse events (SAEs), adverse device effects (ADEs), serious adverse device effects (SADEs), and unanticipated SADEs (USADEs), and by evaluating the frequency and severity of these occurrences.

All data on treatment-emergent adverse events, ADEs, SADEs, and USADEs will be categorized and summarized. The frequency and severity of treatment-emergent AEs, ADEs, SADEs, and USADEs will be summarized for all enrolled participants and the entire duration of the intervention. Adverse events occurring more than once in individual participants will also be summarized and presented descriptively.

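### The safety summary is specified for all enrolled participants, but the safety data set is defined as device-exposed participants; used as a denominator, the wider group lowers device event rates

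*Protocol article*

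**What the plan says.** Two statements in the Statistical analysis section of the Protocol article name different populations for safety.

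- Data analysis set: "The safety data set includes all participants exposed to the biofeedback device". No time limit is attached. The restriction to the first 16 weeks applies to Analysis dataset 1, which serves the efficacy endpoints.
- Safety data: the frequency and severity of treatment-emergent AEs, ADEs, SADEs and USADEs "will be summarized for all enrolled participants and the entire duration of the intervention". The safety data set is not mentioned.

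Three other places decide who is exposed. Under Study design, the treatment arm's 12 weeks begin only with the first completed biofeedback session. The text accompanying Figure 1 adds: "Participants randomly allocated to the waiting list are offered the possibility of entering a 12-week extension phase with biofeedback treatment". Under Randomization and stratification, allocation comes at least four weeks after inclusion, and Study design classes those lost or found ineligible in that interval as screening failures.

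On the event categories, the Safety data paragraph first lists SAEs among the treatment-emergent events collected. It then says: "All data on treatment-emergent adverse events, ADEs, SADEs, and USADEs will be categorized and summarized". SAEs have no place of their own in that sentence, in the frequency-and-severity sentence or in the safety endpoints.

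**The concern.** The article defines a safety population and then specifies its summary of event frequency and severity for a different one. Whoever writes the tables has to depart from one of the two sentences.

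The choice matters because the Safety data paragraph is about events arising during biofeedback training. A person who never used the device cannot have such an event. Adding that person to the denominator leaves the numerator unchanged, so the error can only lower the reported rate. Safety is part of the stated study objective, and the article presents the trial as pivotal, so the incidence of device effects is likely to be quoted from these tables.

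A lesser matter is that seriousness is named only for events also judged device-related (SADE, USADE). A table built strictly from the named categories would have no separate line for serious events judged unrelated, and severity does not convey seriousness.

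**Working it through.** **Inputs**

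- Randomized: 286 (Abstract, Methods: "A total of 286 participants will be randomized to either a 12-week intervention arm or waitlist control arm").
- Sample size assumptions: "Provided an effect size of d = 0.4, a significance level alpha of 0.05 (two-sided), power 0.8", with "a dropout rate of 30% in the post-randomization period" (Statistical analysis, Sample size).
- Allocation ratio: not given. The article says only that "permuted block randomization is performed". I assume 1:1, that is 286/2 = 143 per arm.
- Share of the treatment arm that starts the device, *s*: not given; taken as 1.0, with 0.7 as a variant.
- Waitlist uptake of the device in the extension, *u*: not given; 0 to 1.
- Share of enrolled participants who are never randomized, *f*: not given; 0 and 0.2 shown.

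**Step 1. Does 286 fit equal arms?** A two-sample t-test with d = 0.4, two-sided alpha 0.05 and power 0.8 needs 99.08, so 100 per arm and 200 in total. Dividing by 1 − 0.30 gives 200/0.7 = 285.7, so 286. The normal approximation gives 99 per arm and 198/0.7 = 282.9, so 283. The stated total reproduces with equal arms, which supports the 1:1 assumption without proving it.

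**Step 2. Dilution factor.** The numerator is the same under either rule, so the rate over all enrolled equals the rate over exposed multiplied by

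factor = exposed / enrolled = (143*s* + 143*u*) / (286 / (1 − *f*)).

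**Step 3. Results with *s* = 1**

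| Waitlist uptake *u* | Exposed | Factor, enrolled = 286 | Factor, *f* = 0.2 (enrolled = 286/0.8 = 357.5) |
|---|---|---|---|
| 0 | 143 | 143/286 = 0.50 | 143/357.5 = 0.40 |
| 50% | 214.5 | 0.75 | 0.60 |
| 70% | 243.1 | 0.85 | 0.68 |
| 100% | 286 | 1.00 | 0.80 |

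If only 70% of the treatment arm starts and no waitlist participant takes up the device, exposed = 143 × 0.7 = 100.1 and the factor against 286 is 100.1/286 = 0.35.

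**Step 4. What this means for a reported rate.** Take, purely for illustration, a true incidence of 10% among exposed participants. Over 286 randomized with *s* = 1 it would be reported as 5.0%, 7.5%, 8.5% or 10.0% at uptakes of 0, 50%, 70% and 100%.

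**Step 5. Are SAEs summarized?** The first sentence of the Safety data paragraph places SAEs within treatment-emergent adverse events. The next sentence summarizes all data on treatment-emergent adverse events. SAEs are therefore counted. What is absent is their name in the summary list.

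**The case against.** The strongest reply is that the paragraph states no denominator. Its phrase about enrolled participants may mean coverage, so that nobody's events are dropped. The same paragraph ties the events to biofeedback training and to the duration of the intervention, and a safety set has already been defined, so that set could be taken to supply the denominator. Counting screening failures is a strained reading, since they leave before any device is sent. Detailed methods are left to a SAP that is not shown.

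Part of this stands: dilution follows only if the named group is used as the denominator, and the screening-failure columns above describe a possible reading, not a likely one. It does not remove the conflict. Two populations are stated, and a SAP that follows one must set the other aside.

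A reader might infer that device event rates would be roughly halved. The documents do not support that as a general result. Neither safety sentence excludes the extension, and the whole waitlist arm is offered the device there. A factor of 0.50 against the 286 randomized needs zero uptake, or a summary confined to the randomized 12 weeks. Data lock is allowed while participants are still in the extension, so exposure of the waitlist arm could be incomplete if safety were reported from that lock, but the article does not say that it would be.

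A reader might also infer that SAEs are left out of the summary. That is not supported either, for the reason in Step 5. A separate SAE line is a detail that an article may leave to the SAP.

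**Conclusion.** The point holds as a conflict between two stated populations. If the enrolled group is used as the denominator, device event rates are biased downward whenever any enrolled participant is never exposed.

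The size is open. With 1:1 allocation and every treatment-arm participant starting, the multiplier runs from 0.50 (no waitlist uptake) to 1.00 (full uptake) against the 286 randomized. It is smaller if some treatment-arm participants never start or if screening failures count as enrolled. None of these shares is in the article, so no single figure should be quoted.

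The primary efficacy inference is not affected. The absence of SAEs by name is a minor matter of labelling, not an omission of data.

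**What to change.** In the frequency-and-severity sentence of the Safety data paragraph, replace the reference to enrolled participants with the safety data set defined under Data analysis set. Spell that set out as participants with at least one biofeedback session, including waitlist participants from the time they start the device in the extension.

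As a minor addition, name SAEs in the summary sentence alongside AEs, ADEs, SADEs and USADEs.

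The cost is a change of phrase and one added term, with matching table shells. No new data are needed. The downside is that reported rates become somewhat less favourable. Rates per exposed person-week, or a separate column for unexposed waitlist time, are not needed to resolve the conflict. A waitlist column might also need data that the plan does not clearly collect, since it describes events arising during biofeedback training.

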### Dissemination

The results of this trial will be published in peer-reviewed international scientific journals. The aim is for results to be made available and spread widely to the public, general practitioners, neurologists, and other health professionals who treat patients with headache. The results will be communicated to patients through relevant channels, such as social media, patient organizations, journals for popular science, and appropriate events and conferences.

### Study status

Study start 01.01.2023.

## Discussion

To the best of our knowledge, this is the first pivotal randomized controlled trial (RCT) with an adequate sample size to properly evaluate the efficacy of home-based biofeedback treatment in patients with episodic migraine. A 2022 systematic review of digital headache interventions identified only two RCTs evaluating biofeedback apps for migraine.
^
17
^ Both were pilot studies with small sample sizes and did not show statistically significant between-group differences in important headache related outcomes.
^
9
^
^,^
^
16
^

The uniqueness of Cerebri is that it combines three different biofeedback modalities, whereas traditional treatments typically use one parameter.
^
15
^
^,^
^
18
^ In addition, recent app-based solutions have applied one modality.
^
16
^
^,^
^
19
^
^,^
^
20
^ Different modalities may benefit different users; for example, some users might find it easier to influence their finger temperature, whereas others might prefer muscle tension as their main source of biofeedback. Different modalities also display different responses over time. Finger temperature increases slowly as the user relaxes and lowers their sympathetic tone, whereas muscle tension and HRV respond relatively quickly to activities such as neck shrugging and unpaced breathing, respectively. Together, these varying modalities target different pathomechanisms and potentially embrace more users as individuals often master different forms of autoregulation. The use and combination of these three different modalities have been assessed thoroughly in preliminary studies using a progenitor version of the Cerebri system. First, a feasibility study was conducted to confirm the precision of using surface EMG measured from the skin overlying the upper trapezius fibers to measure neck muscle tension and using a photoplethysmograph placed on the index finger to measure peripheral skin temperature.
^
7
^ Second, a usability study was conducted showing that it is possible to combine the modalities of neck muscle tension, finger temperature, and heart rate to tailor therapist-independent feedback to different users.
^
8
^ Finally, HRV was included as the third parameter instead of simple heart rate measurement, as it was demonstrated in a study from the US,
^
16
^ to be both feasible and acceptable for app-based biofeedback. The non-invasiveness of the Cerebri-system is advantageous in several ways. First, it enables the patients to safely perform the procedure themselves. Second, it means the risk profile is relatively low, with the most severe identified risks being electrical failure in the sensors or charger, skin contact-dependent allergic reactions from the sensor material, and risks related to information security and privacy. All the identified risks were met using an appropriate mitigation strategy. Third, a wider spectrum of patients qualifies for study inclusion; notably, women of childbearing potential who do not use highly effective contraceptives, as well as those who are pregnant or breastfeeding.

The BioCer trial is not blinded and employs a waitlist control. In a previous sham-controlled trial involving adolescents that tested an earlier version of the Cerebri system, the investigators encountered difficulties in developing a biofeedback sham that effectively imitated authentic biofeedback.
^
9
^ False feedback was easily detected by the user, compromising the integrity of the blinding protocol. Conversely, attempts to distort the biofeedback signal by introducing minor “errors” resulted in a sham signal that was “too similar” to true biofeedback, potentially inducing a treatment effect. In addition to the practical challenge of developing an appropriate sham signal, there are significant ethical concerns associated with providing false biofeedback to participants. These concerns include the potential exacerbation of migraines. Indeed, in theory, introducing a false biofeedback signal could lead to mislearning, in which subjects inadvertently adapt incorrect or maladaptive responses based on what they believe to be true biofeedback. Nevertheless, the absence of blinding is a limitation, as it prevents assessment of the placebo effect.

We believe that the effectiveness of Cerebri depends on achieving adequate user satisfaction and adherence to ensure optimal results. However, a recurrent challenge for smartphone-based biofeedback is its low adherence. A pilot study in adolescents of a progenitor version of Cerebri reported poor adherence, with a mere 40% of planned biofeedback sessions completed during weeks 5-8 of the study.
^
8
^ Similar adherence challenges have been reported for smartphone-based systems. In the feasibility study of the current Cerebri system proceeding this trial, biofeedback adherence was also low, declining from 80% in week 1-4 to 20% in week 9-12.
^
11
^ Several usability and software issues were identified and addressed before trial initiation.

To improve the usability of the Cerebri mobile app, additional data were added to the diary and visualized in graphs to provide users with better tools to keep track of their headaches and to compare headache data with biofeedback data directly. In addition, the app content was revised and instructions were improved based on reported use errors or misinterpretations. Based on user insights, the app interface during the biofeedback sessions was tailored to ensure that the biofeedback was performed correctly. Furthermore, the algorithm for calculating the HRV score was modified to compensate for drifting biofeedback scores resulting from frequency leakage from the low-to high-frequency domains of the HR wave. Some drifting still occurs, but it is deemed acceptable as the users are considered unable to observe this.

## Conclusion

Cerebri started as a research project in 2015, with a meta-analysis of the biofeedback literature on adolescents
^
21
^ and concept development on how to enable remote biofeedback for headache patients. The project utilized existing technology in the market, and as the concept developed, custom-made sensors and a more advanced biofeedback app interface were developed over the course of several years. Clinical testing of feasibility and usability continued to show positive feedback from the patients
^
8
^
^,^
^
10
^; hence, the project continued to validate the clinical effect of Cerebri. A feasibility study is important in validating the clinical study setup and defining the final iterations of the Cerebri user interface as the final preparation for this randomized controlled trial on Cerebri.

